### Recruitment

2.10

Recruitment is conducted in several ways. The main recruitment strategy is the online survey of the WHO WMH-ICS. This survey includes several questionnaires measuring the mental disorders and psychological characteristics of the students to be used in epidemiological studies. The e-mail is sent out to first-year students at the Vrije University Amsterdam (VU), and all students at Leiden University, Maastricht University, and Utrecht University and includes information about the Caring Universities project and a survey link. Students receive personalized feedback after completing the survey if they wish. After administering this survey, we invite students who are eligible for inclusion in our study. Volunteer students are informed about the stress management program and asked to give informed consent. Students who do not meet the inclusion criteria will be informed about the possible sources for getting help from other relevant resources (e.g. 113 online, student psychologists, general practitioner (GP), mental health care institutes in the region). Second, we contact the International Office, student clubs, and organizations to reach students with diverse characteristics. Third, we recruit participants through student advisors, student mentors, researchers, and lecturers who can recommend this program for students who might be interested in a stress management program. Finally, we recruit students through advertisements (e.g., flyers, faculty newsletters, social media, related websites, etc.). The advertisements target all college students by informing them about the study and emphasize the importance of stress management programs in increasing well-being and improving academic performance. Students will not be compensated for participation.

### Statistical analysis

2.11

Descriptive statistics will be calculated to examine participants' satisfaction with the intervention, usability, and adherence. We conduct two-tailed paired *t*-tests using a significance level α = 0.05 to assess changes in the scores of PSS-10, PHQ-9, and EQ- 5D5L. In addition, qualitative analysis will be conducted to examine the participants' use of the intervention, their satisfaction with the intervention, adherence, e-coach evaluation, and feedback about the modules. Moreover, semi-structured interviews with the participants will be audio-recorded and the verbal data will be transcribed. After obtaining all of the transcriptions and written responses, a thematic analysis will be conducted to identify and categorize the themes about their experiences with the intervention (Clarke & Braun, 2017). First, we will code and organize the written data under meaningful themes. After categorization of the main themes, we will examine whether they include sub-themes. At the end of the analysis, we will interpret the results based on the themes (Braun and Clarke, 2006; Howitt, 2010).

### Possible harms

2.12

Possible harms can occur when receiving the internet-based interventions (Rozental et al., 2014). Suicide risk would be the most severe possible incident. Some students may show warning signs for suicide while participating in the stress management program. If a suicidal risk is identified by the e-coaches, the suicide prevention protocol will be applied and participation in the study will be terminated. Following this protocol, the e-coach will contact the student and evaluate the suicidal risk by conducting section C of Mini International Neuropsychiatric Interview (M.I.N.I.) (Sheehan et al., 1998). If the e-coach estimates low or moderate suicide risk, the student will be advised to get further help from a GP or 113Online which is a 24/7 accessible online platform designed for talking anonymously about suicidal thoughts. If high suicidality is indicated by the M.I.N.I., we consult with a psychiatrist about the student's specific situation. The student will be immediately referred to a GP or 113Online and closely monitored by the e-coach and the research team. Another risk of receiving this treatment can be related to deterioration (such as worsening stress symptoms), nonresponse, or occurrence of other psychological/ emotional symptoms (Rozental et al., 2014). If these negative effects should be detected, the researchers will report these findings in the manuscript. However, based on the findings of similar studies (Boettcher et al., 2014; Rozental et al., 2015), we anticipate minimal risk for the participants in this study.

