### Study design

2.1

This study is an open trial of a guided internet-based stress management program. It employs a single-group pre- (t0) and post-test (t1) design. Five weeks after t0, t1 is administered. The present study is part of the World Health Organization (WHO) World Mental Health International College Student Initiative (WMH-ICS) (Cuijpers et al., 2019). The study protocol was approved by the Scientific and Ethical Review Board of all participating universities (Vrije University Amsterdam, Leiden University, Maastricht University, and Utrecht University). This study was also registered at the Netherlands Trial Register (Registration Number: NL8686).

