### Sample size

2.9

There is no consensus on how to calculate the sample size of an open feasibility study. Some studies suggest a sample of at least 12 participants (Julious, 2005; Moore et al., 2011) while others recommend 35 or more participants (Teare et al., 2014). Thus, in the present study, no power calculation was conducted to determine the sample size, as we mainly focus on the feasibility and acceptability of the intervention. Based on the rule of thumb and similar previous studies (Rahmadiana et al., 2019), we anticipate that 50 participants will be sufficient to examine our main objectives. For semi-structured interviews, the sample size will depend on the saturation of the codes (Sim et al., 2018). However, we aim to reach at least 10 participants, since it is well-documented that code saturation can be reached after approximately 10 interviews (Hennink et al., 2017).

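### Negative effects are to be reported only if detected, while the one stated quantitative symptom analysis is mean change, which can look favourable while a minority of students worsens

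*Protocol article*

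**What the plan says.** Section 2.12 of the protocol article identifies the harms: "Another risk of receiving this treatment can be related to deterioration (such as worsening stress symptoms), nonresponse, or occurrence of other psychological/ emotional symptoms". Its reporting commitment follows: "If these negative effects should be detected, the researchers will report these findings in the manuscript". The section gives no criterion by which a student would be classed as worsened or as a non-responder.

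Section 2.11 gives one quantitative analysis of symptoms: "We conduct two-tailed paired *t*-tests using a significance level α = 0.05 to assess changes in the scores of PSS-10, PHQ-9, and EQ- 5D5L". The qualitative analysis listed there covers how the programme was used, satisfaction, adherence, the e-coach and the modules. Harm is not among its topics.

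Three further places bear on the point:

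- **Section 2.1.** "It employs a single-group pre- (t0) and post-test (t1) design", and "Five weeks after t0, t1 is administered".
- **Section 2.12, on suicide risk identified by the e-coaches.** "the suicide prevention protocol will be applied and participation in the study will be terminated".
- **Section 2.8.4.** Interviewees are drawn from students who finish all main modules. Individual PSS-10 change is one selection factor, and some students with little or no improvement are chosen.

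**The concern.** Worsening and nonresponse on a symptom scale are properties of individual students. They become visible only when someone sets a threshold and counts. A rule that makes reporting depend on detection, next to an analysis that summarises only the mean, leaves two different situations looking the same in print: nobody worsened, or nobody counted. A manuscript that followed the plan to the letter could be silent on individual deterioration and still comply.

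This matters because the programme is newly developed, is offered to students selected for high stress, and is guided by psychology students. How many participants got worse is among the first things a later trial team will want to know. The students most likely to be affected may also be under-represented in the two places where individual experience is examined. The paired tests need a post-test score, and the interviews need completion of all main modules.

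**Working it through.** There is no figure in the plan to reproduce here. Section 2.9 states that no power calculation was done and sets the target by rule of thumb: "we anticipate that 50 participants will be sufficient to examine our main objectives". The question is therefore whether a clearly favourable paired t-test is compatible with a material share of students worsening. All scenarios below are illustrations.

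**Inputs from the document:** n = 50 (section 2.9); PSS-10 SD 6.2 (section 2.4, a general-population reference and not this trial's sample); two-sided α = 0.05 (section 2.11).

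**Assumed inputs:** effect sizes, within-group SD, pre-post correlation and scale reliability. None of these is in the document.

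**1. Two-group mixture.** A share w worsens by 6 points and the rest improve by 5, with within-group SD 4.

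Mean improvement = 5(1 − w) − 6w; variance = 4² + w(1 − w) × 11²; t = mean / (SD/√50).

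| Worsened | Mean improvement | SD | t | p |
|---|---|---|---|---|
| 5 of 50 (10%) | 3.90 | 5.19 | 5.32 | 2.6 × 10⁻⁶ |
| 8 of 50 (16%) | 3.24 | 5.68 | 4.03 | 0.0002 |
| 10 of 50 (20%) | 2.80 | 5.95 | 3.33 | 0.0017 |
| 15 of 50 (30%) | 1.70 | 6.44 | 1.87 | 0.07 |

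Under these assumptions the test still favours the programme clearly when one student in five worsens.

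**2. Normal model.** SD of change = 6.2 × √(2(1 − r)), with mean improvement 3 points.

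| r | SD of change | t | Any worse score | Worse by 5 or more |
|---|---|---|---|---|
| 0.3 | 7.34 | 2.89 | 34% | 14% |
| 0.5 | 6.20 | 3.42 | 31% | 10% |
| 0.7 | 4.80 | 4.42 | 27% | 5% |

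Part of this spread would be measurement error, which is why a threshold is needed before anyone is called worsened.

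**3. Scale of a threshold.** Reliable change = 1.96 × 6.2 × √(2(1 − reliability)). For assumed reliabilities of 0.80, 0.85 and 0.90 this gives 7.7, 6.7 and 5.4 PSS-10 points. The document supplies neither a reliability nor an SD for the enrolled population, so the limit could move.

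**4. Leaving out terminated students.** Suppose k of 50 are terminated after worsening by 6, and the others improve by 3 on average. The mean over all 50 is [3(50 − k) − 6k]/50 = 3 − 0.18k, against 3.0 among those analysed. The overstatement is 0.18 points for k = 1, 0.36 for 2, 0.54 for 3 and 0.90 for 5.

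**5. Precision of a count.** The exact 95% interval for 5 of 50 is 3.3% to 21.8%. For 0 of 50 the upper limit is 1 − 0.025^(1/50) = 7.1%. These widths follow from the sample size, so they do not support the point itself. They show how a count should be read.

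**The case against.** The strongest reply is that this is a condensed article. A deterioration threshold, missing-data rules and the denominator of a responder table commonly sit in a full protocol or analysis plan that is not shown. That stands: their absence alone is not the finding. The finding is the conditional rule as printed, which would need rewording even if a threshold exists elsewhere.

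It can also be said that the sentence in section 2.12 is a promise to report, and that detection there simply means occurrence. This is a fair reading. The plan does show willingness to disclose harm, and nothing in it makes reporting depend on a favourable mean. A reader might infer that harm is meant to be hidden; the text does not support that.

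A reader might infer that nothing in the plan could reveal worsening. That goes too far. Section 2.8.4 uses individual PSS-10 change scores to choose interviewees, section 2.8.2.1 collects a weekly PSS-4, the Discussion has e-coaches following progress, and the t-tests are two-tailed. None of these yields a rate, however. The interviews are purposive and limited to students who complete all main modules, section 2.11 states no analysis of the PSS-4, and two-tailed testing detects only mean worsening.

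A reader might also take it as stated that terminated students have no post-test. The document says their participation ends. It does not say that the post-test is withheld, that they go uncounted, or that their scores changed most. Section 2.4 excludes suicidal risk and PHQ-9 scores above 20 at entry, so few terminations may occur.

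Finally, symptom change is secondary here, and a single group cannot show that the programme caused any deterioration. Both are correct. They limit the weight of the point without removing the case for a count.

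**Conclusion.** The point holds as one of reporting and analysis choice, and it should be corrected. The plan names individual-level harms, reports them only conditionally, and states a single quantitative symptom analysis that does not count them. Under the illustrative assumptions, a clearly significant mean improvement coexists with 10% to 20% of students worsening. Those shares are not predictions for this trial.

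Averaging over students who worsen is the larger part of the problem. The loss of terminated students from the paired tests is probable but inferred. It shifts the mean by about 0.2 to 0.4 PSS-10 points for one or two such students, if each had worsened by 6 while the rest improved by 3. The documents do not support a conclusion that harm will in fact be concealed or that the programme is unsafe.

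**What to change.** Replace the conditional sentence in section 2.12 with an unconditional commitment, and add one descriptive table to section 2.11:

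- For all enrolled students, give the number and percentage, with exact 95% confidence intervals, showing worsening, no reliable change and improvement on PSS-10 and on PHQ-9.
- Fix the criterion before the data are examined, for example a reliable change index, and state the SD and reliability it uses for each scale.
- Show missing post-test, and termination of study participation for suicide risk, as separate categories kept in the denominator.
- Report the table even when the worsening count is zero, with its upper confidence limit.
- State that the single-group design permits deterioration to be counted but not attributed to the programme.

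The cost is one table and a few sentences, from pre-test and post-test scores and termination records the study already holds. No additional assessment is needed, and no change to the suicide-risk procedure or any other part of the care pathway is implied.

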## Discussion

3

The present study aims to examine the feasibility and acceptability of an internet-based stress management program for college students with elevated levels of stress. In addition, this study will examine whether any improvements in stress levels, quality of life, and depression occur from pre-test to post-test. We anticipate that the stress management program will be perceived as feasible and acceptable by college students. Improvement in the stress, quality of life, and depression scores are also expected after receiving this program, but may not reach significance levels. Similar stress management interventions for college students showed promising results (Frazier et al., 2015; Harrer et al., 2018). However, internet-based stress management programs for pre-selected students with high levels of stress are scarce in the literature. Therefore, we believe that this study will be informative for the development and implementation of internet-based programs for at-risk students in tertiary education. In addition, stress and coping are closely associated with mental health problems such as depression and anxiety (Bergdahl and Bergdahl, 2002; Garnefski et al., 2002). Therefore designing stress management programs for college students can also be preventative for common mental health problems.

Although drop-out rates can be higher in internet-based interventions than face-to-face (Wagner et al., 2014), we have incorporated the suggested strategies from previous studies into our stress management program to increase adherence, such as adding human support (Conley et al., 2013; Mohr et al., 2011) and sending automatic reminders (Hilvert-Bruce et al., 2012). In order to maintain adherence, e-coaches will monitor the progress of participants, and send individualized reminders for the participants when they are inactive on the platform. Also in case of two weeks of inactivity, participants will receive automated reminders. Moreover, we have conducted several focus groups with college students to meet the specific needs of college students in our program. Based on this co-creation approach, we could tailor the content and the features in the platform specifically toward college students. Therefore, it is expected that this stress management program will be engaging and highly acceptable for college students. We also designed this stress management program based on the transactional theory of stress and coping by incorporating CBT components. In a recent meta-analysis, CBT-based interventions yielded a greater effect size than interventions from other theoretical backgrounds (Regehr et al., 2013; Harrer et al., 2019). Another meta-analysis also showed that CBT-based internet interventions were highly acceptable and engaging (Andrews et al., 2010). In view of the results of these studies, we expect similar results in the present study.

We also acknowledge the limitations of the present study. First, we target 50 participants for this study based on other similar work. The sample size will be informative for us to examine the feasibility and acceptability of this program; however, larger sample sizes can yield more robust results. Therefore, if we can reach more than 50 participants, we will include them in the analysis. Second, dropout can be higher in internet-based interventions. Although adding human support to the internet-based interventions was associated with lower dropout rates (Richards and Richardson, 2012), participants may discontinue the program for different reasons such as finding the program complicated, lack of time, or feeling a need for face-to-face contact (Johansson et al., 2015). Third, students will be guided by psychology students. Limitations may arise from the limited experience of the e-coaches, however, they will be supervised by researchers and clinical psychologists in this study. Fourth the generalizability of the results to non-college peers or older adults may be another limitation. Lastly, the PSS-10 and the SUS-10 have been administered in previous studies in the Netherlands. However, we could not retrieve the published psychometric characteristics of these scales in the Dutch language. In addition, the ceiling effect was reported for EQ-5D-5L in the general population (Abdin et al., 2013) and this might exist for college students in this study. Finally, we do not focus on measuring the stressors of college students in this study, as our main objective is to investigate the feasibility and acceptability of this program. Therefore, future studies are needed to explore the nature of the stressors and their associations with perceived stress in more detail.

## Conclusions

4

Despite the limitations, internet-based stress management interventions can be feasible and acceptable for college students. We expect that the findings of the study will be informative for designing psychological interventions and developing cutting-edge mental health applications in higher education.
